### CardioMEMS system

The CardioMEMS HF system includes an implantable wireless sensor with delivery catheter, a patient and hospital electronics system and a patient database (Integrated Merlin.net website for patient data management) [16]. The sensor measures PA pressure using MEMS (micro-electromechanical systems) technology and requires neither battery nor leads (wireless). The sensor is implanted in a branch of the left PA via a transvenous catheter inserted through the femoral vein. The sensor is 15 mm in length, 3.4 mm in width and 2 mm thick. The sensor remains in the PA as a permanent implant which endothelialises completely (Fig. 2). A 4-week course of acetylsalicylic acid and clopidogrel is recommended in those patients without anticoagulation or platelet inhibition [16]. Clinicians are informed about the daily CardioMEMS-derived PA and PA trends over time via Merlin.net (diagnostic tool in disease management). A study operating procedure will be available for clinicians to help them guide HF therapy, most importantly based on a significant rise in PA pressure over time, aiming for normal PA pressures avoiding progressive clinical congestion, or additionally, a significant fall in PA pressure over time avoiding chronic hypovolaemic triggers. The device is FDA approved and CE marked for use in chronic HF patients in NYHA class III and with one HF hospitalisation in the previous year (NYHA classes, Tab. 3).

**Fig. 2 Fig2:**
[figure not shown]
**a** The CardioMEMS sensor (with permission of Abbott Inc.). **b** The CardioMEMS HF system patient unit including antenna (with permission of Abbott Inc.). **c** Location of the CardioMEMS sensor in the left pulmonary artery (with permission of Abbott Inc.)

**Table 3 Tab3:** New York Health Association classification of heart failure symptoms

NYHA class I	Cardiac disease, but no symptoms and no limitation in ordinary physical activity, e.g. no shortness of breath when walking, climbing stairs etc
NYHA class II	Mild symptoms (mild shortness of breath and/or angina) and slight limitation during ordinary activity
NYHA class III	Marked limitation in activity due to symptoms, even during less-than-ordinary activity, e.g. walking short distances (20–100 m). Comfortable only at rest
NYHA class IV	Severe limitations. Experiences symptoms even while at rest. Mostly bedbound patients

### Standard care

In patients with HFrEF, standard care is defined as treatment according to the recommendations in the national and ESC guidelines for HF with up-titrating recommended HF therapies to maximum tolerated or optimal dosages and to evaluate the patient for an ICD/CRT‑D when indicated [23]. For HFpEF (and HFmrEF) treatment recommendations are lacking, but in accordance with the 2016 ESC guidelines it is advised to focus on optimal management of comorbidities and cardiovascular risk factors such as hypertension and atrial fibrillation [23]. All Dutch hospitals have a structured HF outpatient clinic with specialised HF nurses who are supervised by a cardiologist with experience or specific interest in HF treatment. At these outpatient clinics, patients are seen for the up-titration of HF drug therapies at frequent intervals to reach optimal or maximum tolerated dosages of evidence-based medication. Treatment choices are at the discretion of the physician. Further, patients are counselled, e.g. about the aetiology of their HF, diet, fluid and salt restrictions, as well as the importance of treatment compliance and of abstaining from tobacco use and minimising alcohol consumption. Patients are instructed when to contact the outpatient clinic in case of alarming symptoms or abnormal weight gain. After hospital discharge, patients are generally seen by the HF nurse within 2 weeks, and we estimate that patients visit these outpatient clinics on average 3 times/year to see the nurse and at least 2 times/year to see the cardiologist depending on their clinical need and ongoing therapeutic decisions.

### Hypothesis

We hypothesise that the CardioMEMS HF system applied in addition to standard care will improve QoL and reduce HF hospitalisations in patients with chronic HF.

### Clinical study

#### Inclusion window/enrolment

The planned inclusion phase is 24 months. Twenty centres have initially been selected to start including patients in this study. In anticipation of a stable inclusion rate, we calculate a mean inclusion rate of 0.7 patients per centre per month to reach a sample size of 340 patients in 2 years. Patient inclusions are competitive between centres. If, at 6 months, the inclusion rate is lower than 50% of that expected, the number of sites can be increased, if necessary.

#### Duration of follow-up

All patients will be followed for at least 12 months, resulting in a minimum follow-up of 12 months (for the last patient included) and a maximum follow-up of 36 months (for the first patient included) according to the above-mentioned enrolment schedule. The follow-up visits are scheduled at 3, 6, and 12 months and every 6 months thereafter (Fig. 3).

**Fig. 3 Fig3:**
[figure not shown]
The MONITOR HF trial follow-up scheme. Randomisation at baseline visit

#### Patient visits

At baseline demographics, medical history and medication use are evaluated. An echocardiogram is part of the baseline visit (type of HF) as well as a detailed laboratory assessment, QoL questionnaires (Kansas City Cardiomyopathy Questionnaire (KCCQ) and EQ-5D-5L) and a 6-min walk test (6MWT) [24, 25]. During follow-up visits, an electrocardiogram (ECG) is recorded in all patients, NYHA class is established, and a physical examination is performed, including vital parameters and standard laboratory assessments, which will consist of renal function and natriuretic peptides (NT-proBNP or BNP). Serum samples are stored at regular intervals for a biobank at Durrer Center for Cardiovascular Research. A 6MWT is performed at baseline, 6 and 12 months of follow-up. Serial echocardiography is performed at baseline, 12 months and 24 months of follow-up. The KCCQ is performed at baseline, 3, 6 and 12 months, EQ-5D-5L at baseline, 3, 6, 12 and 24 months of follow-up. An iMTA Medical Consumption Questionnaire (iMCQ) for health care utilisation and health technology assessment (HTA) analyses is performed prospectively at 3, 6 and 12 months [26]. Changes in medication and reasons for change are recorded in a detailed logbook. In another detailed logbook, information on patient contacts is recorded, including the reason for contact, direction of contact and location (telephone, general practitioner, outpatient clinic, emergency ward, clinic).

### Outcome measures

#### Primary endpoint: Change in QoL as assessed with the KCCQ HF questionnaire

The KCCQ questionnaire is conducted at baseline (*t* = 0), and at follow-up intervals of 3, 6 and 12 months’ follow-up after randomisation in both treatment arms. Primary analysis is based on change in KCCQ scores at 12 months (Tab. 4). The KCCQ questionnaire assesses QoL in HF patients and has undergone extensive validation in HF populations [27, 28].

**Table 4 Tab4:** Study endpoints

Primary endpoint	Quality of life as measured by the KCCQ HF questionnaire at 12 months’ follow-up
Secondary endpoint	The number of HF hospitalisations during follow-up
	Health status as measured by the EQ-5D-5L questionnaire

*KCCQ* Kansas City Cardiomyopathy Questionnaire, *HF* heart failure

#### Secondary endpoints

The number of HF hospitalisations during follow-up, defined as an unscheduled admission for HF longer than 6 h and/or the need for intravenous diuretics for decongestion of the patient.Change in health status as assessed with the EQ-5D-5L questionnaire.

Other endpoints will be all-cause mortality; all-cause hospitalisations; scheduled HF hospitalisations, composite of all-cause mortality and cumulative HF hospitalisations; cardiovascular mortality; days alive outside of the hospital; days in hospital; emergency ward visits (or equivalent), composite of HF hospitalisations and emergency ward visits for HF, change in NYHA class, health care utilisation, number of patient contacts, change in baseline PA pressure; number of medication changes.

### Statistical analysis

#### Sample size

The conditional coverage agencies requested 90% power on QoL endpoints and at least 85% for the secondary endpoint HF admissions in order to have adequate estimates of effect sizes for cost-effectiveness analyses (which are dependent on this set of variables). We decided to aim for 90% statistical power to detect an at least 6‑point difference in KCCQ overall summary (KCCQ-OS) score between randomised treatment groups [27]; we calculated, at an alpha level of 0.05 and standard deviation (SD) of 15, group sizes of *N*_1_ 133 and *N*_2_ 133 patients (total sample size 266 patients). With an anticipated 10% withdrawal rate, we will need to include 292 patients in total. For the secondary endpoint of HF admissions, we used two assumptions of estimated treatment effect size and estimated event rates of HF hospitalisations in the Netherlands. The long-term results of the CHAMPION trial, more comparable to our follow-up length, showed a reduction of 33% in HF hospitalisations compared to controls (182 HF hospitalisations vs 279 HF hospitalisations, in 270 and 280 patients treated with CardioMEMS vs standard care, respectively; average follow-up 18 months) and the Dutch COACH trial provided an event rate of 2.03% per month in a comparable but slightly less sick cohort of chronic HF patients [16, 17, 29]. Under these assumptions, at least 85% statistical power at an alpha level of 0.05, and a treatment effect size of CardioMEMS of 33% and event rate of 2.0% per month in the control group, when *N*_1_ 164 and *N*_2_ 164 patients, a total of 328 patients is to be included. For the secondary endpoint, EQ-5D-5L improvement in health status, 90% statistical power to detect a significant difference of 0.06 at an alpha level of 0.05 and SD 0.18, a sample size of *N*_1_ 155 and *N*_2_ 155 totalling 310 patients is needed, and by including a 10% early withdrawal rate a total sample size of 340 patients is to be included. Therefore, the total sample size of the trial required to adequately answer the research questions is 340 patients.

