#### Data analysis

Data will be summarised using univariate statistics (number, mean, standard deviation, median) or frequency (number, percentage). For baseline characteristics, between-group comparisons will be performed with the χ2 test for categorical variables and two-sample *t*-tests for continuous variables. The primary time-point for effectiveness analyses on improvement of QoL is 12 months. Change in the KCCQ-OS from baseline to 12 months will be compared between the intervention and standard care groups. Additionally, a linear mixed-effects model will be used to compare change in the KCCQ-OS over time between the randomly allocated treatment groups to account for missing data and longitudinal trends. The effect of CardioMEMS in comparison to standard care in changes of KCCQ clinical summary and KCCQ-OS scores is compared using repeated measurement analysis of covariance adjusted for baseline KCCQ score. EQ-5D-5L scores will be analysed in a comparable manner. The secondary endpoint in the study is the number of HF hospitalisations during follow-up. A Cox proportional hazard regression model with Anderson-Gill method for recurrent events will be used for analysis of clinical events (HF hospitalisations, mortality rates). Additionally, Cox proportional hazard models are implemented to analyse time to first events, including mortality and hospitalisation. Hospitalisation rates and mortality rates are estimated using the Kaplan-Meier method, and *p*-values are computed using the log-rank test. All reported analyses are performed using the intention-to-treat principle. All statistical tests will be 2‑sided with a significance level of 0.05.

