### Strengths and limitations

The current trial is important as it is the first randomised clinical trial in Europe comparing haemodynamic remote monitoring by CardioMEMS with a control group in chronic HF. The trial is adequately powered to test the efficacy of CardioMEMS (in addition to standard care) in improving QoL and reducing HF hospitalisations as compared to standard care. Additionally, this trial will provide further contemporary data with CardioMEMS in addition to the CHAMPION trial and post-marketing registries. As randomisation is essential in efficacy studies (but lacking in post-marketing studies), the current European trial is the first with a control group of standard HF care after the US CHAMPION trial. This MONITOR HF trial will not have a sham procedure in consultation with the MEC and patient councils for a variety of reasons. A sham procedure and sham measurements every day during 3 years of follow-up was deemed unethical with a futile risk, patient efforts and costs. Furthermore, we argue that daily sham measurements (with the sensor turned off, but with its costs) are not a part of current standard care and would impact the true comparison with standard care as it is actually delivered. We recognise that the lack of a sham procedure may introduce a potential bias in the standard care arm. However, this effect can be of any magnitude, direction and degree for each individual patient, either positive or negative (as the technique is most likely not suited for all), and therefore it will be complex to completely quantify the placebo effect (and directions). We will keep precise track of medication changes in response to abnormal readings of PA pressure and HF admissions as well as detailed records of health care utilisation rates, to provide objective proof of subjective improvements. Finally, despite the mentioned limitations, proactive monitoring and interventions based upon pre-symptomatic pressure shifts are needed to achieve any actual sustained benefit of the device. The design of the current trial and the involvement of HTA experts from the start of the project ensures high-quality data for future cost-effectiveness analyses and modelling from a Western European perspective, including detailed health care utilisation data.

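### The stated 85% power for HF hospitalisations does not match the planned recurrent-event analysis; on the article's own rate and effect it is about 60–65% at best

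*Protocol article*

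**What the plan says.** The Sample size section gives 164 per group (328 in total) for HF hospitalisations, at "at least 85% statistical power at an alpha level of 0.05", with "a treatment effect size of CardioMEMS of 33% and event rate of 2.0% per month in the control group". It explains that the coverage agencies asked for at least 85% power here because the cost-effectiveness work depends on the estimate. The control rate is tied to a Dutch study: "the Dutch COACH trial provided an event rate of 2.03% per month in a comparable but slightly less sick cohort of chronic HF patients". The effect size comes from total hospitalisation counts in the US trial: "182 HF hospitalisations vs 279 HF hospitalisations, in 270 and 280 patients treated with CardioMEMS vs standard care", over an average of 18 months. Neither the formula nor the follow-up length behind 164 is given.

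Secondary endpoints defines the outcome as the number of HF hospitalisations during follow-up. Data analysis says: "A Cox proportional hazard regression model with Anderson-Gill method for recurrent events will be used for analysis of clinical events", with Cox models for first events in addition, and "All statistical tests will be 2‑sided with a significance level of 0.05". Inclusion takes 24 months, "resulting in a minimum follow-up of 12 months (for the last patient included) and a maximum follow-up of 36 months". The final size of 340 is reached through EQ-5D-5L (310 plus withdrawal). Strengths and limitations concludes: "The trial is adequately powered to test the efficacy of CardioMEMS (in addition to standard care) in improving QoL and reducing HF hospitalisations".

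**The concern.** A comparison of two proportions counts each patient once, as having had an event or not. The endpoint here counts every admission. If a monthly rate of 2.0% is multiplied by 24 and treated as a proportion of 0.48, the variance used is 0.48 × 0.52 = 0.25. A Poisson count with mean 0.48 has variance 0.48, and more if patients differ in their underlying risk. A sample size built on the smaller variance overstates the power of the analysis that will be run.

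This is a secondary endpoint, but its power was requested by the coverage agencies and is asserted in the article's conclusions on design. If the real figure is near 60%, a true 33% reduction would be missed about four times in ten under the stated assumptions. A non-significant result could then be read as evidence of no effect in a coverage decision.

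**Working it through.** **Inputs.** Two-sided alpha 0.05, power 85%, control rate 2.0% per month, reduction 33% (rate ratio 0.67), 164 per group, final total 340 (170 per group): Sample size and Data analysis. Accrual 24 months, follow-up 12 to 36 months: Inclusion window/enrolment and Duration of follow-up. *Derived, not stated:* with uniform accrual, and ignoring death and dropout, mean follow-up is (12 + 36)/2 = 24 months.

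**1. Reproducing 164.** Take p1 = 24 × 0.02 = 0.48 and p2 = 0.48 × 2/3 = 0.32. With unpooled variance:

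n = (1.960 + 1.036)² × (0.48 × 0.52 + 0.32 × 0.68) / 0.16² = 8.978 × 0.4672 / 0.0256 = 163.9, i.e. 164 per group, with power 85.0%.

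Using exactly 33% (p2 = 0.3216) gives 168. A rate of 2.03% with a ratio of 0.67 also rounds up to 164. Variants that do not give 164 include:
- continuity correction: 180–183
- linear proportions at 18 months: 266
- linear proportions at 12 months: 458
- exponential proportions at 24 months: 245 or 350

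**2. Events needed for the planned analysis.** D = 4 × (1.960 + 1.036)² / (ln 0.67)² = 4 × 8.978 / 0.1604 ≈ 224.

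**3. Events expected with 328 patients.** 164 × 0.48 + 164 × 0.3216 = 78.7 + 52.7, about 131.

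**4. Power with 328, no overdispersion.**
- Wald: SE = √(1/78.7 + 1/52.7) = 0.178; Φ(0.4005/0.178 − 1.96) = Φ(0.29) = 61%.
- Schoenfeld: Φ(√131.5 / 2 × 0.4005 − 1.96) = Φ(0.34) = 63%.

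**5. Power with 340, and with overdispersion.** For n per group, control mean μ1, treated mean μ2 and gamma variance k between patients (k is an assumption; the article gives none), Var(ln RR) = (1/μ1 + 1/μ2 + 2k)/n. At 24 months, 1/μ1 + 1/μ2 = 2.083 + 3.109 = 5.193.

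| Patients | Mean follow-up | k | SE | Power (Wald) |
|---|---|---|---|---|
| 340 | 24 months | 0 | √(5.193/170) = 0.175 | 63% (Schoenfeld 65%) |
| 340 | 24 months | 0.5 | √(6.193/170) = 0.191 | 56% |
| 340 | 24 months | 1 | √(7.193/170) = 0.206 | about 50% |
| 340 | 36 months for all | 0 | √(3.462/170) = 0.143 | 80% (Schoenfeld 82%) |

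A simulation with follow-up uniform on 12–36 months agrees at 340: 63% with no overdispersion, and 56% and 49% with k = 0.5 and 1.

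**6. First-event analysis.** At 2.0% per month as a hazard, about 106 first events are expected with 328 patients and 110 with 340. Power is about 52–56%.

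**7. Withdrawal.** The 328 carries no allowance, although the KCCQ and EQ-5D-5L calculations use 10%. If withdrawn patients contributed nothing, 340 × 0.9 = 306 would remain, with power 58–60%. If they leave on average halfway, the effective size is 153 + 17/2 = 161.5 per group and power is about 61–62%.

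**8. What would give 85% with 340 over 24 months.**

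| k | Control rate (reduction 33%) | Reduction (rate 2.0%) |
|---|---|---|
| 0 | 3.3% (Schoenfeld) to 3.4% (Wald) | about 42% |
| 0.5 | about 5.1% | about 45% |
| 1 | about 10% | about 48% |

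The overdispersed rows solve the variance formula in step 5 for 85%. At 3.3% per month, power is only 73% with k = 0.5 and 63% with k = 1.

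**The case against.** The strongest reply is that the article does not say what its event rate counts, how 164 was obtained or what follow-up was assumed, and that it condenses a fuller protocol. That stands as to origin: the two-proportion source is an inference from an exact numerical match, and the inputs are not uniquely identified. The contradiction does not depend on it, because the stated rate, effect and analysis fall short of 85% even with 36 months for everyone.

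Second, 2.0% may be conservative, since it comes from a slightly less sick cohort. The US control counts imply 279/(280 × 18) = 5.5% per month. At that rate 340 patients would have about 97% power without overdispersion, and 76–87% with k = 1 to 0.5. This also stands: a reader might infer that the trial is underpowered whatever happens, and the documents do not support that. But the plan did not assume the US rate, and the Discussion expects a lower Dutch one. A power statement has to hold under its own assumptions.

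Third, giving withdrawn patients no follow-up is too pessimistic for a recurrent-event analysis, so the loss from withdrawal is small. Finally, the agencies are said to have requested 85%, not to have made it a condition, and the closing claim is of adequate power without a figure.

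**Conclusion.** The 85% figure is wrong for the analysis the article plans. At 2.0% per month, a 33% reduction and a derived mean follow-up of about 24 months, power is 61–63% with 328 patients and 63–65% with 340. These are best-case values that assume no overdispersion. Under an assumed gamma variance of 1 to 0.5, power with 340 is about 50–56%, and withdrawals lower it a little further. Death, which also shortens follow-up, is ignored throughout.

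A reader might go on to infer that 340 is too few for the trial as a whole. The documents do not support that: 340 was set by EQ-5D-5L, and the primary KCCQ calculation asks for 292. The error is confined to the power claimed for HF hospitalisations, and to how a null result on that endpoint would be read.

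**What to change.** In Sample size, replace the claim of at least 85% for HF hospitalisations with the power that 340 patients deliver under the recurrent-event analysis. Suggested wording: about 60–65% at best, conditional on a control rate of 2.0% per month, a 33% reduction and a mean follow-up of about 24 months, and lower with overdispersion (about 50–56% for a gamma variance of 1 to 0.5). Name the formula and the follow-up assumed, and say how withdrawal is treated.

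If thresholds for 85% are given (about 3.3–3.4% per month, or a reduction of about 42%), label them as no-overdispersion figures and print the values under overdispersion beside them. In Strengths and limitations, qualify the adequate-power statement for HF hospitalisations.

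The cost is wording in two sections and in what is reported to the coverage agencies, with a less favourable figure. Enrolment, the planned analysis and the primary endpoint stay as they are.

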### Randomisation

At the baseline visit, patients will be randomised in a 1:1 ratio for standard care plus CardioMEMS PA monitoring versus standard HF care with written and signed informed consent. Crossover is not allowed per study protocol and leads to termination of the patient’s participation in the study. After randomisation, the sensor is to be implanted within 3 weeks per protocol in those randomised to CardioMEMS and a second informed consent form will be signed for use of the Merlin.net website.

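### The EQ-5D-5L sample size of 155 per group matches only a one-sided test; under the plan's two-sided 0.05 rule it gives about 83% power, not 90%

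*Protocol article*

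**What the plan says.** The Sample size section opens with the funders' requirement: "The conditional coverage agencies requested 90% power on QoL endpoints and at least 85% for the secondary endpoint HF admissions". For the primary endpoint (KCCQ overall summary score) it takes a 6-point difference, SD 15, alpha 0.05 and 90% power, giving 133 per group (266 in total, 292 with 10% withdrawal). For EQ-5D-5L it claims "90% statistical power to detect a significant difference of 0.06 at an alpha level of 0.05 and SD 0.18" with 155 per group, 310 in total. It then states that "by including a 10% early withdrawal rate a total sample size of 340 patients is to be included", and 340 becomes the size of the trial.

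The section does not say whether alpha is one- or two-sided. The Data analysis section does: "All statistical tests will be 2‑sided with a significance level of 0.05". Allocation is equal (Randomisation section: "patients will be randomised in a 1:1 ratio").

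**The concern.** With a difference of 0.06 and SD 0.18 the standardised effect is one third. A two-sided 5% test with 90% power needs roughly 190 per group for an effect of that size, so 155 looks too small. If the test is two-sided, as the Data analysis section requires, the stated 90% power cannot be right.

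Three things make this more than a slip in a secondary calculation. EQ-5D-5L gives the largest of the three sample sizes and so fixes the trial at 340. The funding agencies asked for 90% power on the QoL endpoints, and the text presents that request as met. EQ-5D-5L is also the utility measure that the Cost-effectiveness analysis section relies on.

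**Working it through.** **Inputs, all from the Sample size section unless noted.** Difference 0.06; SD 0.18; alpha 0.05; power 90%; 155 per group; withdrawal 10%. Two-sided testing comes from Data analysis and 1:1 allocation from Randomisation.

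**Formula.** n per group = 2 × (z_alpha + z_power)² × (SD/difference)², with (0.18/0.06)² = 9 and z_power = 1.282. Each result was also checked with the exact t-test.

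**1. Reproducing the plan's figure.** One-sided alpha 0.05, z_alpha = 1.645:

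2 × (1.645 + 1.282)² × 9 = 154.1; t-test 154.8, rounded up to **155**. This is the plan's number.

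**2. The test the plan specifies.** Two-sided alpha 0.05, z_alpha = 1.960:

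2 × (1.960 + 1.282)² × 9 = 189.1, rounded up to **190** (t-test 190.1, strictly 191). That is 380 evaluable patients, 70 more than the 310 stated.

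**3. Cross-check on KCCQ.** Difference 6, SD 15, 90% power. Two-sided: 132.3 by t-test, rounded up to 133, the plan's figure. One-sided: 107.7, or 108. The two QoL calculations quote the same alpha of 0.05 but match different sidedness.

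**4. Two-sided power for EQ-5D-5L (t-test, difference 0.06, SD 0.18).**

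| Evaluable per group | How it arises | Power |
|---|---|---|
| 155 | the plan's evaluable number | 83.3% |
| 153 | 340 × 0.9 = 306, halved | 82.8% |
| 170 | all 340 evaluable | 86.5% |

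Even with no withdrawals the power is below 90%.

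**5. What 306 evaluable patients can detect with 90% two-sided power.** A difference of 0.067 at SD 0.18; or a difference of 0.06 if the SD were about 0.16.

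**6. Withdrawal step.** To end with N evaluable after 10% loss, N must be divided by 0.9.

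- EQ-5D-5L: 310/0.9 = 344.4, so 345. The stated 340 is close to 310 × 1.1 = 341 and leaves 306 evaluable, fewer than the plan's own 310.
- KCCQ: 266/0.9 = 295.6, so 296. The stated 292 is close to 266 × 1.1 = 292.6.
- Full 90% power for EQ-5D-5L: 380/0.9 = 422.2, so 423 randomised.

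**7. Effect on the primary endpoint.** KCCQ power at 153 per group (difference 6, SD 15, two-sided) is 93.7%.

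**The case against.** The strongest reply is that 83% applies to an unadjusted comparison. The Data analysis section plans a repeated-measures analysis of covariance adjusted for baseline for KCCQ and says EQ-5D-5L will be handled similarly. If 0.18 is the SD of a single score rather than of a change, baseline adjustment alone would raise the power. The document gives no correlation, so the range must be assumed. At 153 per group, two-sided power would be about 86% for a baseline-to-follow-up correlation of 0.3, 89% for 0.4, 90% for 0.45 and 92% for 0.5. This stands as a limit on what can be said about the power of the final analysis. It does not rescue the stated figure: the sample-size text claims no such gain, and its inputs give 155 exactly by a plain one-sided calculation.

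Other points deserve weight:

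- The document never says the calculation was one-sided; that is an inference. The shortfall under a two-sided test is not, because it follows from the stated inputs and the stated testing rule.
- EQ-5D-5L is a secondary endpoint. Table 4 calls it health status and keeps the term quality of life for KCCQ, so the agencies' request might be read as not covering it. The plural in that request, and the plan's own choice of 90% for EQ-5D-5L, favour the reading that it does.
- The cost-effectiveness result comes from a decision model, not from an EQ-5D-5L significance test. Lower power there means a less precise utility input, not a failed analysis.
- The withdrawal slip is small. For EQ-5D-5L it lowers power from 83.3% to 82.8%; for KCCQ it has no consequence, because 340 exceeds 296.

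**Conclusion.** The concern holds. On the plan's own inputs and its two-sided rule, 155 per group gives 83.3% power, and 82.8% after the planned 10% withdrawal from 340. The stated 90% would need 190 per group, about 23% more than 155. These figures assume an unadjusted two-sample comparison in which 0.18 is the SD of the quantity analysed, which is all that the sample-size text describes. A baseline correlation of about 0.45 would bring power back to 90% at 153 per group, but the plan neither states nor claims one.

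The statement needs correcting because it sets the trial size and presents the agencies' 90% request as met. The primary endpoint is unaffected. The withdrawal arithmetic is a minor additional error.

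**What to change.** Keep the total at 340 and correct the Sample size text:

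- State that alpha is two-sided in each calculation.
- Replace the EQ-5D-5L claim with one of two equivalent statements for 306 evaluable patients at two-sided 0.05 and SD 0.18: about 83% power for a difference of 0.06, or 90% power for a difference of 0.067.
- If a gain from baseline adjustment is to be relied on, state the assumed correlation, its source and the resulting power.
- Divide by 0.9 for withdrawal: 345 for 310 evaluable and 296 for 266 evaluable. Say that 340 leaves 306 evaluable.
- Add that KCCQ power is about 94% at 153 per group, so that the primary endpoint is seen to be secure.

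The cost is wording only: no endpoint, analysis or recruitment target changes. One stated power becomes less favourable, and the funding agencies should be told that, on the stated inputs, EQ-5D-5L does not reach the 90% they asked for on QoL endpoints.
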